## Abstract

**Background:**

Older adults with intellectual disability have high rates of lifestyle**-**related illness yet remain poorly engaged in physical activity and nutrition interventions. There is a need to clarify what types of healthy lifestyle interventions are feasible and effective to implement in this population and how outcome measures can best be tracked. This paper describes the pilot feasibility study protocol for implementing a 12-week physical activity and healthy eating program, ‘Get Healthy!’ with older adults with intellectual disability.

**Methods:**

The primary study aims are to assess the feasibility of implementing and monitoring the ‘Get Healthy!’ program with adults with mild to moderate intellectual disability, aged 40 years and over, and their carers. Secondary study aims are to assess the impact of the intervention across the following parametres: body mass index**,** waist circumference**,** cardiovascular fitness**,** physical activity (amount and intensity) and sedentary behaviours**,** resting blood pressure**,** functional strength/capacity**,** dietary intake (energy intake, food group consumption and diet quality)**,** dietary and physical activity knowledge**,** and quality of life. Between 8 and 10 participants in total will be recruited into the 12-week program that will be run in metropolitan NSW, Australia. A combination of objective and subjective measures will be used to assess program feasibility and impact at set timepoints (baseline, mid and end-program).

**Discussion:**

Results from the feasibility pilot will be used to refine the study methodology and ‘Get Healthy!’ program content for future use in a sufficiently powered trial. Findings may be of interest to a broad range of disability and allied health workers engaged in supporting and monitoring healthy lifestyle change in adults with intellectual disability.

**Trial registration:**

ACTRN: ACTRN12618000349246. Registered March 8, 2018- Retrospectively registered, UTN: U1111-1209-3132.

## Background

Modifiable lifestyle-related behaviours contribute to illness [1] and premature mortality [2] in people with intellectual disability (ID). Across the lifespan, people with ID are more likely than aged-matched peers to be overweight or obese [3–5]. They are less likely to reach recommended physical activity levels and are more likely to engage in sedentary behaviours [6–8]. Additionally, people with ID tend to be less knowledgeable about healthy eating recommendations and more likely to consume diets that are high in discretionary foods (high fat, sugar, salt foods, low in essential nutrients), particularly as snacks, and low in core foods including fruits and vegetables [9–11]. The increased cardiometabolic risk associated with such behaviours is compounded in this population by side effects of commonly prescribed psychotropic medications [12, 13].

Healthy lifestyle interventions in the general population are growing in popularity and have been shown to be effective in reducing lifestyle risk [14–16]. However, despite an increased cardiometabolic risk profile, people with ID remain poorly engaged in preventative care programs [17] including healthy lifestyle interventions [18]. Unlike the progressive decline in the absolute number of cardiovascular related deaths in the general population, there has been no similar decline among people with ID [19], suggesting that health promotion messages and interventions have not yet effectively engaged this population. Rates of potentially modifiable morbidities such as diabetes, high blood pressure, hyperlipidaemia, some cancers, dental decay, malnutrition and osteoporosis remain alarmingly high among people with ID [17, 20–22]. As well as having a significant impact on physical wellbeing, experiences such as being overweight or having dental decay can also lower an individual’s self-esteem and sense of psychological wellbeing [23, 24].

Many barriers exist for people with ID who seek to access healthy lifestyle programs to address these risks. These include lack of transport; lack of funding; stigma, a workforce that is insufficiently equipped to tailor interventions to the unique needs of this population; cognitive, behavioural and communication challenges; and a lack of universal design in urban planning that prevents some people with co-morbidities from accessing public exercise areas [1, 25, 26]. Compared to the robust knowledge base detailing healthy lifestyle interventions in the general population, i.e. [27], less is known about the efficacy of lifestyle interventions for people with ID [28]. Recruitment challenges and the additional complexities of obtaining ethics approvals to include people with ID in clinical trials [29, 30] mean that this population has been underrepresented in healthy lifestyle trials to date. Information about how outcome measures can best be tracked across trials are also lacking as many measurement tools have not been validated in this population.

The small number of ID specific physical activity and healthy eating intervention trials reported in the literature to date has resulted in improvements in fitness and psychosocial functioning [31]. Potential for weight loss appears most likely when both physical activity and nutrition needs are addressed simultaneously [32] within a comprehensive health behaviour education program [31]. Making interventions person centred, facilitating carer involvement [10], providing a higher frequency of session and level of support and sufficiently tailored content, design and delivery also appear to improve effectiveness [33]. For example, Melville and colleagues’ [34] intervention that used a combination of behavioural change techniques, carer involvement and physical activity and nutrition-related supports, produced significant decreases in weight, waist circumference and sedentary behaviours for participants with ID.

Results from published ID lifestyle interventions have not been uniformly successful, however, and further research is needed to clarify the type, intensity and delivery mode of interventions that would be most likely to consistently produce positive change in this population [35]. Hamilton and colleagues review of weight loss interventions in this population, for example, find that while most provided evidence for weight loss during active phase, the evidence for long-term weight loss maintenance is less clear [10]. They also note that some interventions appear to produce a smaller degree of weight loss than would be expected in the general population. Other interventions, however, have found that weight loss interventions can be equally effective for people with and without ID [36]. Controlled physical activity trials for adults with ID such as *Walk Well* [33] did not produce any changes from baseline, despite the parent program’s proven efficacy in the general population. The *Steps To Your Health* trial [37] likewise reported no statistically significant difference in mean moderate-vigorous physical activity level or BMI compared to controls. Further studies that robustly measure physical activity levels and dietary intake are needed to clarify the essential components of best practice lifestyle intervention delivery to this population.

Particularly lacking are studies exploring the impact of healthy lifestyle interventions on older people with intellectual disability. Advances in healthcare and public policy have produced significant improvements in longevity for people with ID [38], yet little is known about how health promotion messages and interventions can best be targeted to this growing demographic. Older people with ID experience higher rates of both physical and mental health morbidities than the general population and are vulnerable to premature ageing, often as early as in their forties, as well as stigma, poverty and social isolation [19]. Targeting lifestyle-related behaviours such as physical activity has been identified as potentially the most impactful single intervention to improve health outcomes for people with ID [39], including the ageing population [1].

### Background to the ‘Get Healthy!’ program

Figure 1 summarises the development process for the ‘Get Healthy! Program, a 12-week healthy lifestyle program designed to support the health promotion needs of older adults with mild to moderate ID. The program provides tailored nutrition and physical activity education as well as guided physical activity sessions in a small group setting. As shown, the structure and content of the program were developed through a combination of expert consultations, systematic literature reviews and stakeholder consultation with managers, carers and people with ID aged 60 years and older. The stakeholder consultation process highlighted the importance of addressing both environmental, person related and organisational barriers when planning a healthy lifestyle intervention. Participants highlighted a preference for group interventions that offered opportunities for social interactions, while carers emphasised the importance of ensuring interventions are adequately resourced to meet the complex needs of clients. Detailed findings from the stakeholder consultations are reported elsewhere [40].

**Fig. 1 Fig1:**
[figure not shown]
Development of the ‘Get Healthy!’ program. The project steering committee members invited to provide feedback were [name], [name], [name], [name], [name], [name], [name], [name], [name], Assoc. [name], [name], [name] and [name]. Additionally, nutrition and exercise physiology student researchers [name], [name], [name], [name], [name], [name], [name] and [name] contributed to the program design

A summary of physical activity and nutrition content, and session structure, as well as required equipment, is provided in Table 1. Participants in the ‘Get Healthy!’ program engage in a minimum of three contact hours each week, for a continuous 12-week period. Contact hours are made up of two 1-h physical activity sessions, held on non-consecutive days, and 1 h per week of guided nutrition information and support. In order to decrease participant time and transportation burden, we will run the weekly nutrition session immediately before or after one of the exercise sessions. Participants will therefore only need to attend the program on two out of 7 days per week. The physical activity component of the program is delivered by an accredited exercise physiologist, and the nutrition-related component of the program is delivered by an Accredited Practicing Dietitian. Both of these program leaders have previous experience running interventions for people with intellectual disability. Intervention intensity and advice is tailored to the individual needs of each participant; however, the program is ideally delivered in a small group setting (three to six people per group). The program can be run in a number of settings; however, access to specialised exercise and monitoring equipment is required for pre- and post-testing as well as some of the physical activity sessions*.* In order to support sustained behaviour change post-intervention, the exercise physiologist will also provide examples throughout the program of accessible and low-cost ways to increase physical activity without specialised equipment.

**Table 1 Tab1:** ‘Get healthy!’ curriculum content

Component	Time commitment	Topics	Resources required^a^
Nutrition	12-week program consisting of the following: One face-to-face 60 min session per week Plus additional follow-up phone calls/prompts during food intake monitoring periods. Phone calls will be made either directly to the participant or to their carer depending on the person’s level of independence.	The style of presentation will be tailored to the abilities of participants. The nutrition *education* component will be presented to all participants and will cover the following topics: • The five food groups • Discretionary foods and healthy snacks • Healthy drinks • Portion size and mindful eating • Eating out choices • Shopping/eating out tour	Equipment: • Scale • Stadiometre • Cameras for each participant • 24-h proxy food recall form • Folder for each participant to keep their handouts • White board • Computer and projector Handouts: • Instructions to complete 3-day digital photography food record • 12-week challenge checklist • ID-adapted Australian dietary guidelines • Nutritional goals and barriers • Weight and BMI • Information about discretionary foods, fruits and vegetables. • Information about the grain, meat and dairy food groups • Healthy snack choices • Are you drinking enough water? • Drink ideas • Healthy plate model, hunger scale and mindful eating • Healthier eating/takeaway options • What to think about when eating out • Healthy Eating Graduate certificate
Physical activity	12-week program consisting of the following: Two 60-min face-to face sessions per week on non-consecutive days. Breakdown of components within each session: - 10% didactic information - 40% aerobic exercise - 30% strength-based exercise - 20% balance-based exercise	The physical activity *education* component will cover the following topics: • What it means to be healthy • Consequences of obesity • Physical activity and screen time guidelines • Appropriate goal setting • Planning for maintenance and self-management • Barriers to Physical activity and how to address them The physical activity *practical* component will be comprised of a combination of aerobic and strength- and balance-based exercise. Types of exercises and exercise intensity to be tailored to abilities and interests of each participant but may include activities such as: cycling on a stationary bike, walking, supported row, horizontal squat, stair climbing, tandem, body weight exercises such as wall push-ups, light dumbbell work.	Equipment: - GTX3+ accelerometres for each participant - Blood pressure Sphygmomanometre and stethoscope - Scale - Stadiometre - Measuring tape - Stationary bikes (including a Monark resistance-based ergometre) - Heart rate monitors - Stop watch - Trundle wheel - Medicine balls - Parallel bars - Stairs - Boxing equipment - Chairs - Exercise mats - Cones - Dumbbells - Horizontal squat machine - Supported row machine - Rower Handouts: - ‘Goal setting’ - ‘Counting our steps’

^a^Handouts listed here are for participants with mild to moderate intellectual disability. They may be modified further depending on the needs of individual participants. Carers participating in Program A will be offered the same information in handouts tailored to their level of health literacy

Based on findings from the literature that the physical activity and nutrition behaviours and beliefs of carers strongly influence those of people with ID [41] and that carers can effectively support healthy lifestyle change for adults with ID [42] the ‘Get Healthy!’ program includes two parallel protocols for engaging carers as co-participants. Carer protocol A allows carers to participate for the same number of sessions as participants with ID and covers the same content. Carer A participant sessions will be run separately to the sessions for people with ID so as to more effectively tailor teaching resources to the different learning needs of both groups. Carer protocol B allows carers who lack time or capacity to engage in the full program to access elements of the program in a more flexible way. This may include attending exercise or nutrition sessions with the participant with ID when able, as well as receiving written information about healthy eating and physical activity. All pathways to participation are summarised in Fig. 2.

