Recruitment and screening: Participants will be recruited from a defined target area in metropolitan NSW, Australia. Intellectual disability service and housing providers, partner organisations and peak bodies within the target area will be approached to advertise the study. Potential participants meeting inclusion criteria will undertake a multi-stage screening procedure prior to enrolment. The screening pathway is outlined in detail in Fig. 2 and includes the following:I.Obtaining informed consent from the person or proxy consent from their next of kin or guardian as required by law. Capacity to provide consent will be based on a combination of carer/disability service provider feedback and research team assessment.II.Completion of the Exercise and Sports Science Australia (ESSA) adult pre-exercise screening tool [43] (carer participants—protocol A). Participants with ID also to complete, with some modifications including tool to be completed in conjunction with qualified exercise physiologist and carer where relevant, language in tool has been simplified to increase accessibility, addition of a screening question for people with Down’s syndrome related to spinal cord compression or atlantoaxial instability, and all participants with ID to be referred for medical clearance irrespective of screening tool results.III.Obtaining medical clearance to participate (all participants with ID, as well as all carer program A participants with a positive score on stage 1 of the ESSA screening tool). The research team will offer to reimburse costs relating to attending the medical clearance appointment.

If we have a greater number of people applying for the trial than we have spaces available, we will consider factors such as gender (with the aim of ensuring both men and women are represented in the sample) and age (preferentially recruiting participants who fall into our target range of 40 years and over).

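### Carer screening is stated for protocol A only, although protocol B carers may attend exercise sessions; an optional one-sentence fix would cover any carer who exercises

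*Protocol article*

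**What the plan says.** The section 'Background to the Get Healthy! program' describes "two parallel protocols for engaging carers as co-participants". Protocol A carers follow the same number of sessions and the same content as the people with intellectual disability (ID), but in sessions of their own. Protocol B is for carers who cannot commit to all of that, and it allows them "to access elements of the program in a more flexible way". The next sentence gives examples: "This may include attending exercise or nutrition sessions with the participant with ID when able". The paragraph ends by referring to Fig. 2 for the participation pathways.

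Under 'Study population', the recruitment and screening paragraph sets out three steps, introduced by: "The screening pathway is outlined in detail in Fig. 2 and includes the following". Step II is the ESSA "adult pre-exercise screening tool [43] (carer participants—protocol A"), with a modified version for participants with ID. Step III is medical clearance for all participants with ID, "as well as all carer program A participants with a positive score on stage 1 of the ESSA screening tool". Neither step mentions protocol B carers.

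Table 1 gives the make-up of a 60-minute physical activity session, held twice a week: "10% didactic information - 40% aerobic exercise - 30% strength-based exercise - 20% balance-based exercise".

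**The concern.** The access given to protocol B carers is wider than the stated scope of the screening. They are introduced as co-participants and may come to exercise sessions, yet both carer safety steps name protocol A alone. On the text shown, a protocol A carer doing this kind of exercise is screened first, while a protocol B carer who joins in is not. No reason is given for treating them differently.

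The screen exists to find people who should see a doctor before they exercise. A protocol B carer who would have had a positive stage 1 result could start without that being known. The article says that the pilot will be used to refine the methodology for a larger trial, so the same wording could carry forward to more people.

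**Working it through.** The article gives no figure for this point to reproduce. The check is a comparison of the text, plus simple arithmetic to bound the exposure.

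**Text side by side**

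| Question | Protocol A carers | Protocol B carers |
|---|---|---|
| Described as co-participants? | Yes | Yes (the phrase introduces both protocols) |
| Physical activity sessions | Full number, run separately | May attend those of the person with ID, when able |
| ESSA screen (step II) | Yes | Not named |
| Medical clearance (step III) | If stage 1 is positive | Not named |
| Said not to exercise? | No | No |

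**Bounds on exposure (inputs from Table 1)**

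- Exercise share of a session: 0.40 + 0.30 + 0.20 = 0.90. The other 0.10 is didactic.
- Upper bound per session: 0.90 × 60 = 54 minutes (didactic part: 0.10 × 60 = 6 minutes).
- Upper bound per week: 2 × 54 = 108 minutes.
- Lower bound: 0 minutes, if the carer only accompanies the person with ID.

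The upper bound assumes that the carer comes to both sessions every week and does all of the exercise. That is close to the full exercise component, which protocol B carers are by definition not expected to take on. It is a ceiling, not an estimate.

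**Number of people**

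The sample size paragraph gives 8 to 10 people with ID and carers in total. If that total covers both groups, there are fewer than 10 carers. The number choosing protocol B is not stated and could be zero.

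**Other safeguards in the text**

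- An accredited exercise physiologist delivers the physical activity component ('Background to the Get Healthy! program').
- Exercise type and intensity are adapted to each participant (Table 1).
- An injury or new health problem leads to GP review before the person continues ('Feasibility outcomes', adverse outcomes). This acts only after the event.

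The first two lower the risk. They do not replace a check before exercise, because tailoring works best when a person's risk is already known.

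**The case against.** The strongest objection is Fig. 2. The article refers to it three times for this kind of content: for the participation pathways, for the full inclusion and exclusion criteria of both the ID and carer groups, and for the screening pathway in detail. The figure is lost from the text available here, so its absence cannot be held against the plan, and it may contain a branch for protocol B carers. The three steps are also introduced as what the pathway includes, not as a complete list. A reader might infer that protocol B carers will exercise unscreened. The documents do not support that inference.

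The second objection is that attending a session need not mean exercising in it. Protocol A carers train in their own sessions, while protocol B carers go along to the session of the person they support. If they only accompany or assist, limiting the screen to protocol A is deliberate and correct. The text allows this reading, although the description of both groups as co-participants with access to program elements also allows the other. This is an ambiguity, not a contradiction.

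Third, screening those who commit to the full 12 weeks and not those who drop in is a defensible choice when a qualified professional runs the session and the activities are tailored.

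These objections keep the point conditional and small, but they do not remove it. The two steps say which carers are covered and leave out one of the two groups, so this is more than silence. If Fig. 2 does screen protocol B carers, the wording of steps II and III is too narrow and should be aligned with it. If Fig. 2 says that they do not exercise, the safety concern goes, and the same statement would be useful in the text.

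**Conclusion.** The point holds as a minor, optional participant-safety improvement. The screening scope stated for carers is narrower than the access stated for them. A gap in protection follows only if protocol B carers take part in the exercise and Fig. 2 does not already screen them. Neither condition can be settled from the text available.

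Exposure per protocol B carer lies between 0 and 108 minutes per week and is probably well below the top of that range. A reader might take 108 minutes as the expected exposure, but the article does not say how much these carers exercise, and their limited availability argues against it. The number of carers concerned is small and unstated. Sample size, analysis and the feasibility benchmarks are unaffected.

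**What to change.** In steps II and III of the recruitment and screening paragraph, replace the restriction to protocol A with a rule based on what the carer does. Any carer, under protocol A or B, completes the ESSA screen before first taking part in exercise, and obtains medical clearance if stage 1 is positive. Add that protocol B carers who only accompany or assist the person with ID are exempt. Check that Fig. 2 says the same.

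This works under either meaning of attending, because it applies only to carers who exercise. It costs one or two sentences, a short questionnaire already in use for protocol A carers, and an occasional clearance visit for a few people. Step III already provides for the expense of such visits: "The research team will offer to reimburse costs relating to attending the medical clearance appointment". The drawback is a small extra burden on carers who chose protocol B because their time is limited.
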